#### Voluntary discontinuation

Participants are free to discontinue their participation at any time. Participants who discontinue from the study will always be asked about the reason(s) for their discontinuation and about the presence of any adverse events. All adverse events will be followed up until resolution or the participant is lost to follow-up.

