#### Reframe IT

The Reframe IT intervention has been described elsewhere [33–35]. In brief, it comprises eight 20-min self-guided CBT modules. It follows the stories of two young people who make video diaries about their day-to-day life and their experience of feeling suicidal. An adult “host” character guides the user through the module and activities. Each module contains two “activities” based on standard CBT exercises. Users progress sequentially through the content, with modules automatically unlocked when the preceding module is complete. There is also a message board through which the participant can communicate with a moderator, a mood diary function, and a series of factsheets and information on local and national helplines and services.

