#### Control intervention

Participants randomised to the control group will receive TAU (e.g. from the school counsellor or external mental health services). The specific nature of TAU will be determined by the wellbeing team at each school. Although this may result in variability in treatment type between sites, the use of TAU as a comparator will facilitate an evaluation of whether receipt of the Reframe IT intervention is associated with improvement over current practice [47]. The wellbeing team at each school will be asked to record what TAU comprised for each student.

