A comprehensive safety protocol has been developed, which will be activated if: (1) participants return a score of 1 or higher on the SIDAS at any time-point (the established cut-off [45] indicating any level of suicidal ideation in the past month); (2) participants report current suicidal ideation at any time-point; (3) participants report suicide risk via the Reframe IT platform. Where possible, the school will be responsible for checking in with the participant and managing any risk, although in some cases researchers will assist with this (e.g. where the school does not have the capacity to follow up with students in a timely way). If this is required, the researcher will contact the participant by phone and conduct a brief risk assessment. The response will depend on the level of risk, and ranges from providing the participant with contact information for helplines (in the case of low risk) to calling the participant’s emergency contact or emergency services (in the case of high-severe risk). All participants will be required to provide emergency contact information via the consent form. Ultimately, all risk information will be communicated to the school, who will be responsible for ongoing management. There are no planned interim analyses for this study, nor are there any stopping guidelines other than as outlined in section “Study discontinuation criteria” of this protocol.

Supervision will be provided to the researchers from the study clinical psychologist, who will also be on call during each assessment session.

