#### Assessment and documentation of AEs

All AEs and SAEs that arise during the trial will be recorded in the study database. The causality of AEs and SAEs (i.e. their relationship to intervention treatment) will be assessed by a suitably qualified study team member. Where possible, information related to causality will be collected from the participant who experienced the adverse event (i.e. whether or not the participant themselves attributes the AE to the intervention) as well as any relevant collateral information from family members, friends, and school staff. Any AE that is serious (i.e. life-threatening) will be reported to the Sponsor and to the relevant ethics committees within 24 hours of the research team becoming aware of its occurrence, regardless of the relationship to the intervention.

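### Between T2 and T3 only the Reframe IT arm has a study channel through which adverse events can surface, so by-arm counts of spontaneously recorded events may be inflated in that arm

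*Protocol article*

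**What the plan says.** All references are to the protocol article.

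- **Aim.** Under Aims and hypotheses, safety is a secondary aim and the absence of iatrogenic effects is a hypothesis.
- **Triggers common to both arms.** Under Safety, supervision, and committees, the safety protocol is activated when "1) participants return a score of 1 or higher on the SIDAS at any time-point" or when "2) participants report current suicidal ideation at any time-point". Table 1 schedules both measures at T1, T2, T3 and T4.
- **Trigger in one arm.** The same list adds "3) participants report suicide risk via the Reframe IT platform". The Reframe IT section describes the platform: "There is also a message board through which the participant can communicate with a moderator, a mood diary function". The eight modules are completed in the 10 weeks between T2 and T3 (Procedure). Controls receive treatment as usual, as decided by each school (Control intervention).
- **Other scheduled questions in both arms.** The four Youth Risk Behaviour Survey (YRBS) items on ideation, plans and attempts are asked at every time point and cover the interval since the last assessment (Additional measures). The full Resource Use Questionnaire (RUQ) at T2, T3 and T4 covers mental health hospitalisation (Secondary outcomes and Table 1).
- **Adverse events as a category.** "All AEs and SAEs that arise during the trial will be recorded in the study database" (Assessment and documentation of AEs). The only direct question described is put to participants who stop voluntarily, who "will always be asked about the reason(s) for their discontinuation and about the presence of any adverse events". Table 1 has no adverse event item.
- **Blinding.** Everyone on the study team except the statistician knows the allocation (Randomisation and treatment allocation). A study team member judges causality.

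**The concern.** Recording events as they come to light gives comparable counts only if both arms have similar opportunities for events to become known. Here they do not. Both arms meet the study at the scheduled assessments, but between T2 and T3 one arm also uses a moderated platform on which a student can disclose distress or risk. The adverse event definition is broad, taking in any unfavourable symptom or deterioration that is associated in time with a study intervention. A disclosure on the message board can thus become a recorded event, while the same experience in a control may go unrecorded.

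Component 2 is the only randomised part of the study, so its between-arm contrast is the only controlled evidence on harm. If spontaneously recorded events are more frequent under Reframe IT, readers could take that as harm, or could dismiss real harm as better detection. The article describes no record of how each event was found, which is what would be needed to separate the two for those events.

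**Working it through.** The article gives no adverse event rate, no detection probability and no by-arm adverse event result, so there is no stated figure to reproduce. The check has two parts.

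**1. Detection routes by arm**

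| Route | Reframe IT | Control |
|---|---|---|
| SIDAS of 1 or more, T1–T4 | yes | yes |
| Current-ideation item, T1–T4 | yes | yes |
| YRBS ideation, plan and attempt items, T1–T4 | yes | yes |
| Full RUQ (mental health hospitalisation), T2–T4 | yes | yes |
| Adverse event question at voluntary discontinuation | yes | yes |
| School contact through treatment as usual | yes | yes |
| Platform with moderated message board, T2–T3 | yes | no |
| Scheduled adverse event question | none stated | none stated |

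One row differs between arms. Treatment as usual does not offset it, because the intervention arm is Reframe IT plus treatment as usual.

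The shared rows leave some room for that difference to matter:
- SIDAS looks back 4 weeks. T2 to T3 is 12 − 2 = 10 weeks, which leaves 10 − 4 = 6 weeks outside its recall. T3 to T4 is 12 weeks, which leaves 12 − 4 = 8. The current-ideation item concerns the moment of asking.
- The YRBS items cover the whole interval, but they are not among the safety triggers, and the article does not say that YRBS or RUQ answers are entered as adverse events.
- Events that are neither suicide-related nor a mental health hospitalisation have no scheduled adverse event question in either arm.

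**2. How large the distortion could be (assumed values only)**

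Let t be the true event rate, equal in both arms; c the share of events found by channels common to both arms; and p the share of the remaining events found by the platform. The 335 randomised students at 1:1 give 335 / 2 = 167.5 per arm.

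- Expected recorded, control: 167.5 × t × c
- Expected recorded, Reframe IT: 167.5 × t × (c + (1 − c) × p)
- Spurious ratio: 1 + p × (1 − c) / c, which does not depend on t

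| c | p = 0.1 | p = 0.3 | p = 0.5 |
|---|---|---|---|
| 0.9 | 1.01 | 1.03 | 1.06 |
| 0.7 | 1.04 | 1.13 | 1.21 |
| 0.5 | 1.10 | 1.30 | 1.50 |

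Example with t = 0.10, c = 0.5 and p = 0.5. Control: 167.5 × 0.10 × 0.5 = 8.4 events. Reframe IT: 167.5 × 0.10 × 0.75 = 12.6 events. The ratio is 0.75 / 0.5 = 1.50.

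A two-sided 5% comparison of two proportions with 167 per arm would show a significant excess in the Reframe IT arm about 15% of the time in that example. Over all settings tried (t of 5%, 10% and 20%) the chance runs from about 3% to 28%, against 2.5% in that direction if recording were equal. With counts this small the normal approximation is rough.

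**The case against.** The strongest reply is that the events that matter most are already asked of both arms on the same schedule. SIDAS, the current-ideation item and the YRBS items go to everyone at T1 to T4, and the full RUQ to everyone at T2 to T4. A sound between-arm comparison of attempts, plans, ideation and mental health hospitalisation can be made from data the plan already collects. That stands, and it confines the point to spontaneously recorded adverse events.

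Four stronger readings are tempting, and the documents do not support them:

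- **That suicide risk is found mainly through the platform, or actively asked about only at discontinuation.** Two of the three triggers are the same in both arms at all four assessments, and the YRBS items add to them. Only adverse events as a category lack scheduled questioning.
- **That discontinuation gives the intervention arm an additional adverse event question.** The question at voluntary discontinuation applies to any participant. The list specific to the intervention group concerns stopping an intervention that controls do not have, and no adverse event question is tied to it.
- **That by-arm counts are biased, by a known factor.** The detection shares above are assumptions. A platform report activates a risk response, and the article does not say that each such report is logged as an adverse event. Every Component 2 student has ideation at entry, and a pre-existing condition counts only if it deteriorates.
- **That the plan commits to a flawed test.** The article states no formal between-arm test of adverse events.

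It is also fair to say that the full safety protocol and the safety committee manual are not shown and may describe a common way of eliciting events. The article nonetheless sets out definitions, triggers, documentation and causality assessment in some detail, and the asymmetry lies in what it states.

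**Conclusion.** The point holds in limited form. Suicide risk and mental health hospitalisation are asked about equally in both arms. Between T2 and T3, however, only the Reframe IT arm has a study channel through which risk or adverse events can come to light, and adverse events as a category are recorded as they arise, by a team that is unblinded apart from the statistician. By-arm counts of spontaneously recorded adverse events may therefore be inflated in the Reframe IT arm.

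The size is unknown. With equal true rates and a platform that finds 10% to 50% of otherwise missed events, the spurious ratio is about 1.01 to 1.06 if common channels find 90% of events, and 1.10 to 1.50 if they find 50%. All of these shares are assumed. The distortion is negligible where the shared questionnaires find most events and material where they do not. The channel is documented for T2 to T3; whether the platform stays open until T4 is not stated.

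**What to change.** 1. State that the between-arm safety comparison, which bears on the hypothesis of no iatrogenic effects, rests on events captured by scheduled instruments that both arms complete: YRBS plans and attempts, RUQ mental health hospitalisations, SIDAS and current ideation.
2. Add one adverse event item, worded identically for both arms, to the T2, T3 and T4 questionnaires, and include it in that comparison.
3. Add a database field for the detection source of each adverse event: scheduled questionnaire, platform, discontinuation, school or other.
4. List platform-detected and discontinuation-detected events separately by arm, outside the main comparison.

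The platform remains a safety route and the safety response stays as it is. The cost is one questionnaire item, one database field and amended wording. The downside is a slightly longer questionnaire and more non-serious events to record. The change does not help for students who miss T3 or T4, so the number completing each assessment should be shown by arm beside the comparison. If the safety committee manual already contains a common elicitation procedure, a sentence in the protocol pointing to it would cover the second step.

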### Adverse events

#### Definitions of adverse events and serious adverse events

##### Adverse event (AE)

An adverse event is the development of an untoward effect, undesirable clinical occurrence or medical condition, or the deterioration of a pre-existing medical condition following or during exposure to a study intervention, whether or not considered causally related to the study intervention. For the purposes of safety reporting, any research activity is considered to be part of the “study intervention”.

An AE can therefore be any unfavourable and unintended clinical sign (including an abnormal laboratory finding), symptom, observation, or disease temporally associated with the use of an intervention, whether or not related to the intervention.

##### Serious adverse event (SAE)

An SAE is any untoward medical occurrence that:
Results in death;Is life-threatening;
Life-threatening in the definition of serious refers to an event in which the participant was at risk of death at the time of the event; it does not refer to an event which hypothetically might have caused death if it were more severe.Requires inpatient hospitalisation or prolongation of existing hospitalisation;Results in persistent or significant disability/incapacity;Is a congenital anomaly/birth defect;Is an important medical event that although not immediately life-threatening or result in death or hospitalisation, based upon appropriate medical and scientific judgement, may jeopardise the participant and/or require intervention to prevent one of the outcomes listed above.

Outpatient treatment in an emergency department is not in itself an SAE, although the reasons for it may be (e.g. suicide attempt).

Hospital admissions and/or surgical procedures planned before or during a study are not considered SAEs if the illness or disease existed (or the surgery was planned) before the participant was enrolled in the study, provided that it did not deteriorate in an unexpected way during the study.

#### Assessment and documentation of AEs

All AEs and SAEs that arise during the trial will be recorded in the study database. The causality of AEs and SAEs (i.e. their relationship to intervention treatment) will be assessed by a suitably qualified study team member. Where possible, information related to causality will be collected from the participant who experienced the adverse event (i.e. whether or not the participant themselves attributes the AE to the intervention) as well as any relevant collateral information from family members, friends, and school staff. Any AE that is serious (i.e. life-threatening) will be reported to the Sponsor and to the relevant ethics committees within 24 hours of the research team becoming aware of its occurrence, regardless of the relationship to the intervention.

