#### Participant withdrawal criteria

A participant will be considered “withdrawn” from the study in cases where all involvement is ceased.

A participant will be withdrawn if:
Participation interferes with appropriate clinical management of risk of harm to self or others (as judged by the school wellbeing staff and/or senior researchers, and in consultation with treating clinicians if appropriate);SAEs occur that could be associated with any intervention included in this study;The participant or their parent or guardian indicates they no longer wish to participate;The participant leaves the school.

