#### Study discontinuation criteria

The study may be terminated by the Sponsor (Orygen) with or without cause.

Discontinuation will be considered in the event that a suicide attempt or death occurs, and it is *reasonably possible* that the attempt or death was caused by any of the interventional components (safeTALK, screening or Reframe IT) of the study. See section “Assessment and documentation of AEs”. for details on determination of causality.

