### Safety, supervision, and committees

The organisational structure of this trial is as follows. The MAPSS steering committee is comprised of the CI, project manager, and clinical supervisor and is responsible for investigator oversight of the MAPSS project. The MAPSS steering committee meet on a fortnightly basis. The MAPSS Safety Monitoring Committee (SMC—Equivalent to the Data Safety and Management Committee (DSMC)) is the main vehicle for safety management, data monitoring, endpoint adjudication, and data management strategy. This committee is comprised of the CI, project manager, as well as independent internal and external subject matter experts including the Sponsor. The composition of the group was designed to incorporate transparency and so that no one set of competing interests could unduly influence other stakeholders, and is appropriate for this non-commercially funded or sponsored study. This committee has a dual safety role: it incorporates a risk-appropriate safety, endpoint adjudication, and data management strategy which is responsive to study issues as they eventuate. The committee meets on a quarterly basis and on an ad hoc basis when deemed necessary by the steering committee. The charter for this committee is outlined in the SMC manual, available upon reasonable request by contacting the corresponding author.

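### The 24-hour reporting rule explains serious as life-threatening, which conflicts with the protocol's own six-criterion SAE definition and leaves the handling of other SAEs unclear

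*Protocol article*

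**What the plan says.** The protocol's adverse event sections do three things that bear on this point.

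- **Definition.** The section on serious adverse events lists six alternative criteria. One reads "Requires inpatient hospitalisation or prolongation of existing hospitalisation". Another begins "Is an important medical event that although not immediately life-threatening or result in death or hospitalisation". Life-threatening is a separate criterion with a narrow meaning: it "refers to an event in which the participant was at risk of death at the time of the event", and hypothetical danger is excluded. The same section notes that a suicide attempt behind an emergency department visit may itself be an SAE.
- **Reporting.** Under Assessment and documentation of AEs, all AEs and SAEs go into the study database and a study team member assesses causality. The timed duty then follows: "Any AE that is serious (i.e. life-threatening) will be reported to the Sponsor and to the relevant ethics committees within 24 hours". The clock starts when the research team becomes aware, and the duty applies whatever the causal relationship.
- **Consequences.** The Study discontinuation criteria state: "Discontinuation will be considered in the event that a suicide attempt or death occurs". A causal condition is attached: safeTALK, screening or Reframe IT must be a reasonably possible cause. No severity threshold is set. The Participant withdrawal criteria require withdrawal if "SAEs occur that could be associated with any intervention included in this study".

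The section on safety, supervision and committees adds that there are no interim analyses and no stopping guidelines beyond the study discontinuation criteria.

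**The concern.** The bracket in the reporting rule equates a class defined by six criteria with one of its members. In most trials that would be a small slip. Here the event most likely to test it is a suicide attempt, which the trial exists to prevent and which its only stopping provision names.

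At stake is whether the Sponsor, which may terminate the study, and the ethics committees must be told within a set time of a serious but not life-threatening attempt. Reporting regardless of relationship also has a purpose of its own. Causality is judged by a study team member, and apart from the statistician the study team is not blinded to allocation. Sending every serious event to outside bodies means their notice does not depend on that judgement. A rule that can be read as covering only life-threatening events weakens this safeguard for the others.

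**Working it through.** No statistical calculation applies. The check compares the reporting trigger with the definition, then looks for any other timed report.

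**Step 1: the six criteria against the 24-hour rule, read literally.**

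| SAE criterion (paraphrased) | Inside the 24-hour rule? | Could apply to a suicide attempt? |
|---|---|---|
| Death | Not named, but plainly meant | Yes, if fatal |
| Life-threatening | Yes | Yes |
| Hospital admission or longer stay | No | Yes |
| Lasting disability | No | Yes |
| Birth defect | No | No |
| Important medical event | No | Yes |

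Inside: 1 named + 1 by sense = 2. Outside: 6 − 2 = 4. Of those four, 4 − 1 (birth defect) = 3 could apply to an attempt. If death is also read strictly, the counts are 1 inside and 5 outside, but no sensible reader would exclude a death.

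**Step 2: one event through the text.** Take an attempt that leads to admission, with no risk of death at the time.

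- It is an SAE by the admission criterion.
- It is not life-threatening as the protocol defines that term.
- If a trial component may have caused it, the study discontinuation criteria and the participant withdrawal criteria both apply.
- On the literal reading, it is outside the 24-hour report. If serious keeps its defined meaning and the bracket is ignored, it is inside.

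**Step 3: is there another timed report to the Sponsor or ethics committees?**

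- Voluntary discontinuation: AEs are followed to resolution or loss to follow-up. This is not a report.
- Safety protocol, as summarised: risk information goes to the school. No time is given for telling the Sponsor or ethics committees.
- Committees: the Safety Monitoring Committee includes the Sponsor and meets quarterly, or ad hoc when the steering committee sees a need. This is a possible route with no deadline for an individual event.

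The published text therefore contains one timed report to these bodies, and its trigger disagrees with the definition it relies on.

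**The case against.** The best defence is that serious is a defined term. Its definition comes immediately before the reporting rule, treats life-threatening as one element, and names a suicide attempt as a possible SAE. On that view the bracket is careless shorthand and every SAE is already reportable within 24 hours. This reading is tenable, so the literal reading cannot be treated as settled. It does not rescue the wording, because a 24-hour duty that supports two readings still needs correcting.

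A second defence is that this is a journal article. It mentions a comprehensive safety protocol and a Safety Monitoring Committee manual, neither shown, and either may set escalation times. That stands against any claim that the trial has no timed report for such events. It does not remove the conflict between two sections of the article itself, which states the restriction and does not merely leave out detail.

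Third, the practical exposure is limited. Deaths and life-threatening attempts are covered, all SAEs are recorded and assessed for causality, and the protection of the individual student runs through the school and the withdrawal rules. This is correct and limits the weight of the point.

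A reader might also infer a delay figure from the line "The MAPSS steering committee meet on a fortnightly basis", setting up to a fortnight against 24 hours. The documents do not support that. A meeting interval is not a reporting deadline, the steering committee (chief investigator, project manager and clinical supervisor) is neither the Sponsor nor an ethics committee, and nothing says its members wait for a meeting to learn of an event.

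**Conclusion.** The point holds as a conflict between the SAE definition and the reporting rule. The literal reading leaves four of six criteria, three of them relevant to a suicide attempt, outside the only timed report to the Sponsor and ethics committees in the published text. The charitable reading leaves an ambiguity under which the same attempt could be reported within 24 hours or only recorded. Either way the trigger does not clearly match the study discontinuation criteria, which set no severity threshold for an attempt.

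The count assumes that death is meant to be included. The number of events affected cannot be estimated, because the protocol gives no attempt rate. The trial's effect estimates are not touched.

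Two stronger conclusions are not supported. A reader might infer that a non-life-threatening attempt has no mandatory timed report at all; the ambiguity and the unseen safety documents rule out that certainty. A reader might also infer that every attempt should carry a 24-hour report. The protocol does not set that standard, and an attempt that does not meet the SAE definition is not part of this inconsistency. The wording should be corrected because the change is cheap and concerns the trial's central safety event.

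**What to change.** In Assessment and documentation of AEs, replace the opening of the reporting sentence, up to and including the bracket, with *Any SAE as defined above*. Keep the 24 hours from the research team becoming aware, the two recipients, and the clause that reporting does not depend on the relationship to the intervention. The study discontinuation criteria need no change.

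The cost is a one-phrase amendment and some additional 24-hour reports for SAEs that are not life-threatening. Their number cannot be estimated from the protocol. No new data collection is needed, since all AEs and SAEs are already entered in the study database. If the Safety Monitoring Committee manual or the safety protocol sets reporting times, they should be checked against the amended sentence.

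Extending the 24-hour report to attempts that do not meet the SAE definition would be a new requirement. Attempts are asked about by questionnaire after baseline in a planned 4020 screened students, so its burden is unknown, and it is not proposed here.
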